# A multicenter, randomized controlled, non-inferiority trial, comparing nasal continuous positive airway pressure with nasal intermittent positive pressure ventilation as primary support before minimally invasive surfactant administration for preterm infants with respiratory distress syndrome (the NIV-MISA-RDS trial): Study protocol

**DOI:** 10.3389/fped.2022.968462

**Published:** 2022-07-29

**Keywords:** nasal continuous positive airway pressure, nasal intermittent positive pressure ventilation, minimal invasive surfactant administration, neonatal respiratory distress syndrome, preterm infants

## Abstract

**Background:**

Non-invasive ventilation (NIV) treatment has been developed to minimize lung damage and to avoid invasive mechanical ventilation (IMV) in preterm infants, especially in those with a gestational age of <30 weeks. Our hypothesis is that for preterm infants <30 weeks with potential to develop respiratory distress syndrome (RDS), nasal continuous positive airway pressure (NCPAP) is non-inferior to the nasal intermittent positive pressure ventilation (NIPPV) as primary respiratory support before minimal invasive surfactant administration (MISA).

**Methods and design:**

The NIV-MISA-RDS trial is planned as an unblinded, multicenter, randomized, non-inferiority trial at 14 tertiary neonatal intensive care units (NICUs) in China. Eligible infants are preterm infants of 24–29^+6^ weeks of gestational age who have spontaneous breaths at birth and require primary NIV support for RDS. Infants are randomized 1:1 to treatment with either NCPAP or NIPPV once admitted into NICUs. If an infant presents progressively aggravated respiratory distress and is clinically diagnosed as having RDS, pulmonary surfactant will be supplemented by MISA in the first 2 h of life. The primary outcome is NIV treatment failure within 72 h after birth. With a specified non-inferiority margin of 10%, using a two-sided 95% CI and 80% power, the study requires 480 infants per group (in total 960 infants).

**Discussion:**

Current evidence shows that NIV and MISA may be the most effective strategy for minimizing IMV in preterm infants with RDS. However, there are few large randomized controlled trials to compare the effectiveness of NCPAP and NIPPV as the primary respiratory support after birth and before surfactant administration. We will conduct this trial to test the hypothesis that NCPAP is not inferior to NIPPV as the initial respiratory support in reducing the use of IMV in premature infants who have spontaneous breaths after birth and who do not require intubation in the first 2 h after birth. The study will provide clinical data for the selection of the initial non-invasive ventilation mode in preterm infants with a gestational age of <30 weeks with spontaneous breaths after birth.

**Clinical trial registration:**

https://register.clinicaltrials.gov, identifier: NCT05137340.

## Background

Although nearly 90% of newly born infants breathe spontaneously within 30–60 s after birth, the remaining 10% of newborns do not breathe within the first 60 s after birth or are persistently bradycardic (1). Because of intrauterine risk factors and the attack of preterm birth, very-low-birth-weight infants may have inhibited respiratory center, poor inspiratory effort, weak intercostal muscles, and poor diaphragmatic function (2). They may require positive pressure ventilation or even advanced resuscitation with an endotracheal tube. With aeration of the lungs, the liquid in the trachea and airways will be cleared and spontaneous breathing is triggered. Pulmonary surfactant (PS) is evenly distributed in the alveoli to reduce surface tension, reduce vascular resistance and improve pulmonary compliance (3). However, the alveolar type 2 cells in very preterm infants are immature, and the secretion of pulmonary surfactant is insufficient to meet the need, resulting in alveolar collapse and progressive exacerbation of dyspnea shortly after birth and in the first 2–6 h (4). Therefore, very preterm infants have the potential to develop respiratory distress syndrome (RDS).

According to the guidelines of neonatal resuscitation, positive end-expiratory pressure provides low positive pressure to the airway, which prevents lung collapse at the end of expiration and maintains functional residual capacity (2). For some very preterm infants, the birth transition process is smooth, and they can have spontaneous breaths after birth. Studies have shown that the immediate start (<15 min after birth) of nasal continuous positive airway pressure (NCPAP) may help to reduce the need for intubation and intermittent positive pressure ventilation (IPPV) in very preterm or very low birth weight infants and to prevent bronchopulmonary dysplasia (BPD) (5, 6). Therefore, it is proposed in the neonatal resuscitation guidelines in 2020 that for very preterm infants with spontaneous breaths after birth, NCPAP, a less invasive respiratory support, should be given, instead of intubation, to keep the lung open and delay the occurrence of lung collapse (2).

At present, NCPAP and nasal intermittent positive pressure ventilation (NIPPV) are the two most common non-invasive ventilation (NIV) modes for the initial respiratory support in NICUs (7). NIPPV imposes no more than 30 times per minute ventilator inflations to a set peak pressure (maximum 15 cmH_2_O) and may be delivered by short binasal prongs to very preterm infants. NIPPV has been used in NICUs for a variety of indications, especially for extubation ventilation support. It could reduce intubation due to frequent primary apnea, asynchronous thoracoabdominal motion, and inspiratory effort, and improve the stabilization of the chest wall and the tidal and minute volumes (8, 9). However, compared with NCPAP, NIPPV might be more invasive and might involve more risks to very preterm infants. An association has been found between the use of NIPPV and the increased risk of abdominal distention, vomiting and gastrointestinal perforation (10, 11). In view of the gentle ventilation support strategy to the tiny, very preterm infants during the birth transition period, there is lack of high-quality evidence to support the superiority of NIPPV to NCPAP.

RDS remains a significant problem for preterm infants, although its management has evolved in the “post-surfactant era”, resulting in improved survival of the very preterm infants (12). The optimal approach to administering pulmonary surfactant (PS) has attracted great attention in neonatology in recent years. The transition from intubation-surfactant-extubation (InSurE) to less-invasive surfactant administration (LISA) and minimally-invasive surfactant therapy (MIST), and the minimal invasive surfactant administration (MISA) with specially designed minimally invasive tubes in China, as well as administration of PS with laryngeal masks and aerosol inhalation, reflects the efforts to minimize lung trauma and the application of gentle ventilation strategy, as much as possible, in the care of very preterm infants in NICU (13, 14).

The updated *European Consensus Guidelines on the Management of Respiratory Distress Syndrome-*−*2019 Update* recommends NCPAP combined with LISA as the main treatment of respiratory distress syndrome (RDS) in preterm infants with spontaneous breaths (6). Unfortunately, there are few large randomized controlled trials to compare the effectiveness of NCPAP and NIPPV as the initial respiratory support mode before MISA in the treatment of preterm infants with RDS. A small-scale prospective cohort study suggests that the efficacy of LISA with NIPPV, in terms of the need of intubation, was not significantly different from that of NCPAP (15). A randomized controlled study shows that NIPPV combined with MIST reduced the need for invasive mechanical ventilation (IMV) within the first 72 h of life in infants with a gestational age of 26–32 weeks when it was compared with NCPAP although the reduction of the need for IMV was not found in the subgroup of infants aged <30 weeks (16). Hence, well-designed and larger randomized controlled studies are warranted for infants with a gestational age of <30 weeks.

The aim of this study is to assess whether NCPAP is non-inferior to NIPPV in preventing NIV treatment failure, when used as primary respiratory support for preterm infants <30 weeks and diagnosed with RDS.

## Methods

### Study design

The NIV-MISA-RDS trial is a multicenter, randomized, non-inferiority trial, conducted in preterm infants <30 weeks' gestational age requiring primary non-invasive respiratory support for respiratory distress in the first 2 h of life. The trial will be conducted in 14 centers and carried out according to the prospective trial flow shown in Figure 1. All hospitals where the participating NICUs are located are midwifery institutions with an annual delivery of more than 3,000 newborns. All the participating NICUs are level three facilities with a more than 50% survival rate of premature infants 24–30 weeks in the past 3 years before the initiation of the study. Before delivery, a multidisciplinary consultation will be made, and a neonatologist will communicate with the family, as premature deliveries at 24–30 weeks involves many risks. A neonatal resuscitation team will be set up before the deliveries for the implementation of neonatal resuscitation with T-piece, non-invasive ventilation for preterm infants with spontaneous breaths. The neonatal resuscitation teams will use the transfer warmer for in-hospital transfer, and will use the T-piece device during transfer until admission of infants into NICUs. All infants will start either NCPAP or NIPPV by ventilators in NICUs after randomization. Pulmonary surfactant will be made available, and once diagnosis of RDS is made, PS will be administered within 120 min after birth. All neonatologists in the 14 centers have routinely taken care of preterm infants with respiratory distress and have used NIV as their standard mode of primary respiratory support. They have been trained for neonatal resuscitation and MISA. Individual practice and team training are required to sustain knowledge and skills.

**Figure 1 F1:**
[figure not shown]
Prospective flow chart of the study. NCPAP, nasal continuous positive airway pressure; NIPPV, non-invasive positive pressure ventilation; GA, gestational age; IMV, invasive mechanical ventilation; NIV, non-invasive ventilation; RDS, respiratory distress syndrome; MISA, minimally invasive surfactant administration; hsPDA, hemodynamically significant patent ductus arteriosus; IVH, intraventricular hemorrhages; BPD, bronchopulmonary dysplasia; NEC, necrotizing enterocolitis; ROP, retinopathy of prematurity.

### Participants

#### Inclusion criteria

Infants who meet all of the following criteria will be included:

Infants of 24–29^+6^ weeks GA.Infants with spontaneous breaths and signs of respiratory distress that will receive non-invasive respiratory support [positive end expiratory pressure (PEEP) of 6 cmH_2_O and fraction of inspired oxygen (FiO_2_) ≤ 0.40] immediately after birth in a delivery room and during transfer to a NICU.They have a clinical diagnosis of RDS within 2 h of life. The diagnosis of RDS will be based on clinical manifestations (respiratory rate > 60/min, nasal flaring, retractions, grunting, or skin cyanosis) and (FiO_2_) > 0.3 for (SpO_2_) > 85%, or the Silverman Anderson Score (SAS) > 5 points, or the SAS increases > 2 points per hour.Parental written consent is obtained.

#### Exclusion criteria

Infants who meet any of the following criteria will be excluded:

Infants who have been intubated prior to pulmonary surfactant administration due to postnatal resuscitation or other reasons.Infants with obvious malformations affecting respiratory function.Infants who have been transferred to other hospitals for surgery or die of other complications with uncompleted data.Infants who have participated in other interventional research.

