### Planned intervention

Preterm infants with spontaneous breaths will be stabilized on non-invasive respiratory support (PEEP of 6 cmH_2_O and FiO_2_ ≤ 0.40) in the delivery room and during admission to NICUs, and then randomly selected to start NCPAP or NIPPV within 30 min of birth.

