### Outcome measures

#### Primary outcome measure

The primary outcome is NIV treatment failure within 72 h after birth, as determined by objective oxygenation, blood gas, and apnea criteria, or the need for intubation and mechanical ventilation.

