### Sample size calculation

The failure rate of NCPAP with MISA approach was 24.5% (of NIPPV, 22.4%) in preterm infants aged <32 weeks with RDS (15). There was no statistical difference between the two groups. We have set the non-inferiority margin for the trial at 10%. That is, NCPAP is supposed to be non-inferior to NIPPV if the difference in risk of NCPAP treatment failure and the upper limit of its bilateral 95%CI is <10%. To demonstrate this with 80% power, 452 infants per study group are required. In order to prevent the loss of samples, the sample size is increased by 6%. Therefore, a total of 960 samples will be selected and allocated randomly 1:1 into the two study groups (480 in the NCPAP group and 480 in the NIPPV group).

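### Exclusion 1 is tied to surfactant instead of randomisation, so an intubation on the assigned mode is both a primary-outcome event and a ground for exclusion

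*Protocol article*

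**What the plan says.** All references are to the protocol article.

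- **Allocation.** The abstract (Methods and design) states: "Infants are randomized 1:1 to treatment with either NCPAP or NIPPV once admitted into NICUs". Planned intervention says that infants are stabilised first "and then randomly selected to start NCPAP or NIPPV within 30 min of birth". Table 1 also places allocation within half an hour of birth, and lists the pre-surfactant assessment as post-allocation.
- **Surfactant.** Study design: "once diagnosis of RDS is made, PS will be administered within 120 min after birth". The MISA method section has it given while the infant is on the assigned mode.
- **Exclusion 1.** "Infants who have been intubated prior to pulmonary surfactant administration due to postnatal resuscitation or other reasons". The abstract's Discussion describes the population in a similar way, as infants "who do not require intubation in the first 2 h after birth".
- **Inclusion 3.** "They have a clinical diagnosis of RDS within 2 h of life".
- **Exclusion 3.** Infants transferred for surgery, or who die of other complications, with incomplete data.
- **Primary outcome.** "The primary outcome is NIV treatment failure within 72 h after birth". Intubation and mechanical ventilation are among the events that count.
- **Analysis.** Outcome data are analysed by original allocation under intention to treat, and Randomization says that it is eligible infants who are assigned.
- **Sample size.** 452 per group for 80% power. To cover losses, "the sample size is increased by 6"%, which gives 480 per group.

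**The concern.** The interval between allocation and surfactant can last 90 min or more, and it is spent on unblinded study treatment. It is also the period the title asks about, namely support before surfactant. An intubation in that interval is a failure of the assigned mode. Exclusion 1 covers it, because the criterion is anchored to surfactant and extends to reasons other than resuscitation.

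Removing randomised infants because they had an outcome event breaks the comparability that randomisation provides. In a non-inferiority trial the damaging case is the one where NCPAP is truly worse and more of its failures come early. Removing them shrinks the observed difference and makes a false claim of non-inferiority more likely.

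Two other criteria share the weakness in part. The RDS diagnosis may be made up to 2 h of life, so in some infants it is settled after allocation, using oxygen need and a distress score that the assigned mode may affect. Transfer or death with incomplete data is likewise known only later in some infants. Every randomised infant who is dropped must also be absorbed by the 6% allowance.

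**Working it through.** **1. The plan's own figure.** Inputs from Sample size calculation: failure 22.4% (NIPPV) and 24.5% (NCPAP), margin 10 points, upper limit of a two-sided 95% CI, power 80%.

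n = (1.960 + 0.842)² × (0.224×0.776 + 0.245×0.755) / (0.100 − 0.021)²
= 7.849 × (0.1738 + 0.1850) / 0.00624 ≈ 451.2, so 452 per group. The stated figure reproduces, and 452 × 1.06 ≈ 480. Power is 80.1% with 452 and 82.4% with 480.

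**2. Effect of the exclusion on the error rate.** Let p be the true 72 h failure risk in an arm. Let e be the share of randomised infants in that arm intubated between allocation and surfactant; all of them are failures. The article does not give e, so every value below is an assumption. With the exclusion applied:

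- analysed risk q = (p − e)/(1 − e)
- analysed n = 480(1 − e)
- P(declare non-inferiority) = Φ[(0.10 − (q_NCPAP − q_NIPPV))/SE − 1.96], with unpooled SE.

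True risks are set at the margin, 22.4% and 32.4%, where the correct error is 2.5%.

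Worked case, 2% and 4%: q_NIPPV = (0.224 − 0.02)/0.98 = 0.2082; q_NCPAP = (0.324 − 0.04)/0.96 = 0.2958; difference 0.0877; n = 470 and 461; SE = 0.0283. Then Φ(0.0123/0.0283 − 1.96) = Φ(−1.525) = 6.4%.

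| Early intubation, NIPPV / NCPAP (assumed) | Analysed difference, points | False non-inferiority |
|---|---|---|
| none | 10.0 | 2.5% |
| 2% / 4% | 8.8 | 6.4% |
| 3% / 6% | 8.1 | 10.0% |
| 2% / 2% | 10.2 | 2.1% |
| 5% / 5% | 10.5 | 1.6% |
| 4% / 2% | 11.9 | 0.4% |
| 10% of each arm's failures | 9.5 | 3.7% |
| 20% of each arm's failures | 9.0 | 5.6% |
| 30% of each arm's failures | 8.3 | 9.0% |

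In the last three rows the same fraction of failures is early in both arms. NCPAP then has more early intubations only because its total risk is higher (for 10%: 2.24% against 3.24%).

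**3. Effect of lost infants on power.** At the design rates, dropping an assumed 10%, 20% or 30% of the 480 leaves 432, 384 or 336 per arm. Power is then 78%, 73% or 68%, against 82.4% with all 480. These figures hold the failure rates fixed. The allowance covers 480 − 452 = 28 infants per arm.

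**The case against.** The strongest reply is that nothing in the article says a randomised infant is taken out of the analysis under exclusion 1. Randomization speaks of eligible infants being assigned, and Outcome data promises analysis by original allocation. Read together, these allow screening at allocation and retention of everyone afterwards. Figure 1, which might settle the matter, is not available here. This stands in part: a reader might infer that the plan definitely deletes early failures, and the text does not prove that. But absence of intubation before surfactant cannot be known at 30 min when surfactant comes later, and the population described in the abstract's Discussion points towards exclusion. What remains is a contradiction over the primary analysis set.

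Three further points stand.

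- It would be too broad to say that eligibility as a whole is decided after randomisation. Gestational age, spontaneous breathing, delivery-room support and delivery-room intubation are known before it, some infants may meet the RDS definition by admission, and excluding intubations that precede allocation is harmless.
- It is tempting to say that the exclusion always pulls the difference towards zero. It does not: equal early rates widen it slightly, and an excess on NIPPV works against NCPAP.
- Larger inflation can be produced. With 3% and 9% the error is 33.5%, but that puts 28% of all NCPAP failures (9/32.4) before surfactant, and nothing in the article supports it.

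Finally, dropping RDS from the inclusion criteria would not be a free remedy. The stated aim concerns infants diagnosed with RDS, and infants who never develop it can dilute the difference. If 20% never develop RDS and never fail (assumed), a 10-point deficit becomes 0.8 × 10 = 8 points, and the chance of declaring non-inferiority is about 11%.

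**Conclusion.** The point holds as a contradiction that affects the primary comparison. Exclusion 1 cannot be reconciled with the allocation time, the primary outcome and the intention-to-treat statement as they are written. If it is applied, the bias depends on early-intubation rates that the article does not give. At a true 10-point deficit the false non-inferiority rate ranges from 0.4% to 10.0% over the assumed rates in the table, against a correct 2.5%. Inflation requires early intubation to be more frequent on NCPAP, which is plausible when NCPAP is truly worse, the case that the test must guard against. The sample size calculation itself is sound: 452 reproduces, and 480 per arm gives 82.4% power if all are analysed.

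**What to change.** 1. Reword exclusion 1 so that it covers only infants intubated before randomisation.
2. Define the primary analysis set as all randomised infants, analysed as allocated. Count every intubation or NIV failure from randomisation to 72 h as a primary event, including those before surfactant.
3. Do not remove randomised infants for later transfer or death, and align exclusion 3 accordingly.
4. Reconcile the abstract (Methods and design, and Discussion), the inclusion and exclusion criteria, and Outcome data on whether RDS must be established before randomisation. Where infants are randomised before the diagnosis, keep them in the primary analysis. Report the RDS/MISA-treated subset as a supporting analysis, and state that infants who never develop RDS may dilute the difference.

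Items 1 to 3 change wording only and leave the 452 per group as it stands at the design rates. Item 4 needs a decision on the target population. If infants without RDS stay in the denominator, the failure rate may be lower than assumed and the difference smaller, so the supporting analysis should be read beside the primary one. Infants intubated early must be followed to 72 h and beyond like all others, because their data cannot be recovered later.

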#### Therapy

The first dose of pulmonary surfactant is 100 mg/kg, and the criteria of repeated use of surfactant are as follows: (1) within 72 h after birth; (2) progressively aggravated respiratory distress after first dose with a minimum interval of 4–6 h; (3) chest X-ray is consistent with the imaging findings of RDS; (4) dyspnea caused by other causes is excepted.

The decision for intubation and IMV within 72 h and 7 days after birth of life is based on the following criteria: (1) severe respiratory acidosis with PaCO_2_ > 65 mmHg and pH <7.2; (2) hypoxemia with SpO_2_ of <0.85 on FiO_2_ > 0.4; (3) recurrent apnea with ≥3 episodes per hour or a single episode of apnea requiring positive pressure ventilation within 24 h; (4) SAS increasing > 2 points per hour, or SAS > 5 points lasting more than 2 h after first or second dose of surfactant administration; (5) pulmonary hemorrhage; (6) cardiopulmonary arrest requiring intubation; (7) neonatologists in the NICU believe that invasive respiratory support should be given to patient. Extubation criteria are established as mean airway pressure (MAP) <8 cm H_2_O and FiO_2_ <0.3.

The decision for weaning of NCPAP or NIPPV is based on the following criteria: (1) the infant has recovered from RDS; (2) the signs of respiratory distress have disappeared and SAS <3 points; (3) when NCPAP with PEEP <3–5 cmH_2_O, or when NIPPV with MAP <6–7 cmH_2_O and FiO_2_ ≤ 25%; (4) without apnea or intermittent hypoxia.

After being assessed by the NICU clinicians to meet all the conditions and lasting for more than 24 h, withdrawal of NIV can be considered.

All of the enrolled infants will be started on caffeine soon after admission at a loading dose of 20 mg/kg followed by a maintenance dose of 5–10 mg/kg.

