### Safety procedures

All eligible infants will be monitored by researchers throughout the study to ensure their safety. Any serious adverse events or important adverse events will be assessed by the neonatologists in each center and by the principal investigator. This study adheres to the principle of subject protection and discontinues the experiment in time if any adverse events occur, regardless of whether they are related to this study or not.

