#### Outcome data

The data will be analyzed based on the original treatment allocation of the participants in accordance with the intention-to-treat principle. To compare the primary and secondary outcomes between the two groups, we will use the Student's *t*-test for continuous variables (if normally distributed), the Mann-Whitney U test (if skewed) and the *chi*-squared test for categorical variables. In addition to the *p*-value of the outcomes, results are to be given in terms of differences and 95% CIs. Preplanned exploratory subgroup analyses are to be performed for the primary and other pre-specified outcomes by gestational age, and birth weight. All data will be analyzed using SPSS version 20.0. Two-tailed *p-*values <0.05 will be considered as statistically significant.

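### Exclusion 3 removes infants after randomisation on the basis of death or surgical transfer, against the stated intention-to-treat analysis, and no outcome counts death

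*Protocol article*

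**What the plan says.** Under Exclusion criteria, the third item excludes "Infants who have been transferred to other hospitals for surgery or die of other complications with uncompleted data". Under Planned intervention, infants are stabilised and "then randomly selected to start NCPAP or NIPPV within 30 min of birth"; the Randomization section places this after arrival in the NICU. Under Outcome data, "The data will be analyzed based on the original treatment allocation of the participants in accordance with the intention-to-treat principle".

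The primary outcome is NIV treatment failure within 72 h of birth, "as determined by objective oxygenation, blood gas, and apnea criteria, or the need for intubation and mechanical ventilation". Of the intubation criteria under Therapy, the one closest to death is "cardiopulmonary arrest requiring intubation". The secondary list has 14 items, from NIV failure by 7 days to costs. Neither that list nor Table 1 has an item for death, mortality or survival. BPD is assessed at a post-menstrual age of 36 weeks, and durations of support and oxygen at discharge.

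The Sample size calculation section assumes failure in 24.5% (NCPAP) and 22.4% (NIPPV), with a margin of 10 points on the upper limit of the two-sided 95% CI. It asks for 452 infants per group, raised by 6% to 480.

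**The concern.** Half an hour after birth nobody can know that an infant will later die of a complication, be transferred for surgery, or have incomplete data. Although it is listed as an eligibility criterion, the rule can in practice act only on infants already randomised, and it selects them by outcome. An infant removed in this way is not analysed as allocated, so the exclusion and the intention-to-treat statement cannot both be followed.

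The rule also does not say which data must be incomplete. An infant with a known 72 h result who is transferred or dies later, and so lacks later data, could lose a valid primary result.

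Because no outcome names death, an infant who dies before 72 h without meeting a failure criterion or being intubated is a non-failure if kept and is absent if removed. Neither describes that result correctly.

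Removal may differ between the arms. The Background associates NIPPV with gastrointestinal perforation, a plausible reason for surgical transfer. The Discussion says that NCPAP fails often. These point in opposite directions, and treating staff are not blinded. At stake is whether the primary non-inferiority conclusion rests on comparable groups.

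**Working it through.** **1. The plan's own figure.** Inputs from Sample size calculation: failure 0.245 (NCPAP) and 0.224 (NIPPV), margin 0.10, one-sided alpha 0.025, power 0.80.

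n = (1.960 + 0.842)² × [0.245×0.755 + 0.224×0.776] / (0.10 − 0.021)² = 7.849 × 0.3588 / 0.006241 = 451.2, so 452 per group. The stated figure is reproduced. Inflation gives 452 × 1.06 = 479.1, so 480. Power at the planned rates is 80.1% with 452 per group and 82.4% with 480. The sample size arithmetic is not in question.

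**2. Effect of removal on the error rate.** Set the truth at the margin: 32.4% (NCPAP) against 22.4% (NIPPV), 480 per arm. Let a fraction e of an arm be removed and a fraction f of those removed be failures. Then:

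- observed risk q = (p − f·e)/(1 − e), with n = 480(1 − e)
- d = q(NCPAP) − q(NIPPV), SE = √[Σ q(1 − q)/n]
- chance of declaring non-inferiority = Φ[(0.10 − d)/SE − 1.96]

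Worked case, 4% v 2% removed, all failures: q = (0.324 − 0.04)/0.96 = 0.2958 and (0.224 − 0.02)/0.98 = 0.2082. So d = 0.0877, SE = 0.0283, and the chance is Φ(0.436 − 1.96) = 6.4%.

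The removal rates below are assumptions, because the article gives none.

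| Removed, NCPAP v NIPPV | Share of removed that failed | Chance of declaring non-inferiority |
|---|---|---|
| none | – | 2.5% |
| 3% v 3% | all | 1.9% |
| 6% v 6% | all | 1.4% |
| 4% v 2% | all | 6.4% |
| 6% v 3% | all | 10.0% |
| 2% v 4% | all | 0.4% |
| 3% v 6% | all | 0.1% |
| 4% v 2% | half | 2.9% |
| 6% v 3% | half | 3.1% |

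**3. Effect of counting early deaths as non-failures.** Here q = p − e with n = 480. If deaths that meet no criterion occur in 1% v 0.5%, the chance is 3.7%. At 4% v 2% it is 10.8%, and at 6% v 3% it is 19.8%. Reversed, 2% v 4% gives 0.4%.

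**4. What it means for a single result.** Suppose the 6% allowance is used up by removals, 480 − 452 = 28 per arm, and the retained infants show 111/452 v 101/452 failures. The difference is 2.2 points, 95% CI −3.3 to 7.7, so non-inferior. Now put the 28 per arm back:

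- all 28 failed in both arms: 139/480 v 129/480, upper limit 7.8; conclusion unchanged
- 28 v 14 failed: 139/480 v 115/480, difference 5.0, upper limit 10.6; non-inferiority lost
- 14 v 28 failed: 125/480 v 129/480, difference −0.8, upper limit 4.8; conclusion strengthened

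An excess of 12 or 13 failures among the removed NCPAP infants is enough to pass 10 points.

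**The case against.** The strongest objection is that the rule is narrow. It covers transfer for surgery and death from other complications, with incomplete data. On that reading, infants with complete data stay in, and an infant intubated or meeting a criterion before death is a failure if retained. The failure criteria are also broad: they include pulmonary haemorrhage, arrest requiring intubation, and the neonatologist's own judgement. Few early deaths would escape all of them. This stands. It limits how many infants are affected, and it makes the larger figures in step 3 unlikely, since they need 19 to 29 NCPAP infants (4% to 6% of 480) to die by 72 h without meeting any criterion. It does not remove the contradiction.

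A second objection is that missing-data methods and death as a competing event for BPD usually belong in the SAP, which is not shown. That is right, and their absence is not the finding. The article itself states the exclusion, the analysis principle and the outcome lists, and these conflict as printed.

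Several stronger readings are tempting but not supported:

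- A reader might infer that the rule favours NCPAP. It does so only if more failures are removed from that arm; equal or reversed removal lowers the error below 2.5%.
- The requirement in Study design that sites have survival above 50% might be read as showing high mortality. It is a floor for site selection, not a 72 h death rate in infants who breathe spontaneously and are not intubated.
- The Safety procedures sentence, which "discontinues the experiment in time if any adverse events occur, regardless of whether they are related to this study or not", might be read as ending follow-up. It does not say whether outcome collection stops. It is a separate point and only needs reconciling with follow-up to discharge in Table 1.
- Deaths need not go unrecorded: serious adverse events are assessed and a monitoring board reviews safety. Death is simply not an outcome.

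**Conclusion.** The point holds in this form. Exclusion 3 acts after randomisation, selects on outcome and contradicts the intention-to-treat statement, and no listed outcome counts death. That the rule acts after randomisation is inferred from the timing and is not said in words, but no other reading is realistic.

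Neither the direction nor the size of the bias can be determined from the article. Across the removal rates tried, with a true difference at the margin and all removed infants failing, the chance of declaring non-inferiority runs from 0.1% to 10.0% against a nominal 2.5%. If only half of the removed infants failed, it stays close to nominal for an excess on NCPAP (2.9% and 3.1%). These figures use a normal approximation and illustrate sensitivity; they do not predict the result. The plan must be corrected before analysis all the same, because removals chosen by outcome cannot be defended afterwards.

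**What to change.** - Delete exclusion 3, so that all randomised infants are analysed as allocated, consistent with the Outcome data section.
- Count death from randomisation to 72 h as failure in the primary outcome.
- Keep transferred infants with their known 72 h status. Where it is missing, run a prespecified worst-case or tipping-point sensitivity analysis.
- Add death before discharge to the secondary outcomes and Table 1, and report death or BPD at 36 weeks beside BPD.
- Separately, reconcile the Safety procedures sentence with the follow-up to discharge in Table 1.

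The cost is mainly wording. The sample size stays at 480 per group, with 82.4% power at the planned rates if all are analysed. Some outcomes after transfer will have to be obtained from the receiving hospital. The composite will include a few deaths unrelated to ventilation mode, and it differs slightly from the endpoint behind the 24.5% and 22.4% planning rates.
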